activity [37]. Importantly, prefrontal-temporal tDCS has been shown to modulate 
dysfunctional network connectivity in patients with schizophrenia, underscoring 
the potential of neuromodulation to target circuit-level deficits [38]. Moreover, 
tDCS not only modulates the activity and connectivity of cortical and subcortical 
brain networks but also influences blood concentrations of biomarkers such as 
brain-derived neurotrophic factor (BDNF) and glial cell line-derived neurotrophic 
factor (GDNF). These systemic alterations collectively form the biological basis 
for its therapeutic effects [39]. BDNF and GDNF function as critical biomarkers 
for synaptic plasticity, a process involved in the pathogenesis and treatment of 
schizophrenia [40]. The hypothesized mechanisms underlying HD-tDCS, particularly 
its enhancement of long-term memory, include the upregulation of BDNF expression, 
activation of its signaling pathway, and improved synaptic plasticity [41]. 
Similarly, studies on CCRT have demonstrated its effectiveness in enhancing 
cognitive function in schizophrenia, accompanied by observed increases in serum 
GDNF levels [42]. Moreover, the literature also proposes that serum BDNF and GDNF 
levels might represent the central nervous system’s BDNF and GDNF expression 
profile [43, 44]. BDNF is essential for neuronal synthesis, 
differentiation, maintenance, and survival. Studies have demonstrated a 
correlation between decreased peripheral blood BDNF levels and cognitive 
impairments, such as attention deficits, in individuals with schizophrenia 
[45, 46, 47]. GDNF levels have been associated with working memory performance and 
attention deficits [48]. As far as we know, no research has investigated the 
combined effects of magnetic resonance imaging (MRI)-guided HD-tDCS targeting 
mPFC and CCRT on cognitive deficits, nor the biological mechanisms underlying 
their combined use in treating schizophrenia.

The current study aims to achieve three primary objectives. The primary aim of 
this study is to evaluate the synergistic effects of HD-tDCS and CCRT on 
cognitive abilities and clinical symptoms through a randomized controlled trial. 
We hypothesize that the combined HD-tDCS and CCRT intervention will result in 
greater cognitive improvement in individuals with schizophrenia compared to 
either intervention alone. The secondary aim is to evaluate the long-term impacts 

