### 2.11 Statistical Analysis Plan

The sample size was calculated using G*Power software (version 3.1.9.7, 
Heinrich-Heine-Universität Düsseldorf, Düsseldorf, Germany), 
employing an F-test and a repeated-measures ANOVA model. In this study, we 
established the probability of a Type I error (α) at 0.05, the 
probability of a Type II error (β) at 0.20, and the statistical power (1 
- β) at 0.80, with an effect size (f) of 0.25. The required sample size 
was calculated to be 36 participants. Accounting for a 20% dropout rate and 
ensuring equal group sizes, the target sample size was determined to be 48 
participants, with 12 participants per group. The calculation of the sample size 
mentioned above is based on the sample size calculation methods adopted in 
previous literature [50]. An article suggests that when designing a preliminary 
study with no prior information for reference, a sample size of 12 participants 
per group is appropriate based on feasibility, improvements in the precision of 
mean and variance estimates, and regulatory considerations [51]. The 
sample size in this study satisfies the previously mentioned criteria and will 
offer enough statistical power to achieve the objectives.

We will utilize histograms and the Shapiro-Wilk test to assess the normality of 
the data distribution. For normal distribution data, continuous variables will be 
reported as mean ± standard deviation, whereas categorical data will be 
presented as frequencies (n) and percentages (%). Statistical tests such as 
one-way analysis of variance (ANOVA), Mann-Whitney U test, *t*-test, and chi-square 
test will be employed to assess baseline differences among groups. In accordance 
with the Consolidated Standards of Reporting Trials (CONSORT) guidelines, all 
analyses will be conducted using the intention-to-treat (ITT) principle, whereby 
participants will be analyzed according to their original randomization group. To 
address missing data within the ITT framework, we will employ linear 
mixed-effects models. These models are appropriate for making valid inferences 
under the missing-at-random assumption and are well-suited for managing the 
unbalanced data resulting from participant drop-out. To specifically assess the 
synergistic effect between HD-tDCS and CCRT, the models will incorporate the 
HD-tDCS × CCRT interaction as a fixed effect. We will conduct 
sensitivity analyses by comparing the results derived from mixed-effects models 

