thinning [74]. Individuals with chronic, untreated schizophrenia exhibit more 
pronounced progressive deterioration of brain structures—such as reductions in 
gray matter volume, diminished white matter integrity, and disrupted brain 
network connectivity—compared to those who have been recently diagnosed or 
treated [75]. These findings suggest that the complex interplay between the 
pathophysiological processes of the disease and its pharmacological management 
may influence the therapeutic efficacy of both HD-tDCS and CCRT. Future research 
should incorporate subgroup analyses based on illness duration to specifically 
investigate how these factors may moderate the interaction between HD-tDCS and 
CCRT.

This study still has some limitations. Firstly, the relatively small sample size 
might influence the statistical power and limit the generalizability of the 
outcomes. Future research should consider increasing the sample size to enhance 
statistical robustness. Secondly, the absence of a double-sham control group, 
which would receive both sham HD-tDCS and a sham version of CCRT, complicates the 
ability to definitively differentiate between specific therapeutic effects and 
potential placebo effects. Additionally, the lack of corresponding sham controls 
for the HD-tDCS-alone and CCRT-alone groups constrains our capacity to accurately 
assess the independent contributions of each monotherapy. Thirdly, we intend to 
collect resting-state fMRI data, which could not provide task-specific 
information. Future study will employ task state fMRI to reflect the fMRI images 
of the brain when performing specific tasks. Finally, the mechanisms underlying 
the combined therapy remain relatively unexplored, particularly regarding how 
these two modalities synergistically enhance cognitive function through specific 
pathways. This necessitates further comprehensive research to elucidate these 
mechanisms.

This study protocol establishes an important theoretical framework for exploring 
the combined therapy and provides guidance for future research. Using MRI-guided 
HD-tDCS targeting mPFC will enhance the development of individualized therapies 
for schizophrenia. Findings from multimodal neuroimaging and blood biomarkers 
could uncover the mechanisms of combining MRI-guided HD-tDCS with CCRT for 
schizophrenia and contribute to develop more individualized approaches. As a 
result, this integrated therapeutic strategy holds significant promise for 

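### The article claims enough power for its objectives, but the calculation behind N = 36 does not power the synergy test or the comparisons with each single therapy

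*Protocol article*

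**What the plan says.** Protocol article, section 2.11, describes a G*Power calculation "employing an F-test and a repeated-measures ANOVA model". It sets the "probability of a Type I error (α) at 0.05" and the "probability of a Type II error (β) at 0.20", "with an effect size (f) of 0.25". The result is 36 patients, raised to 48 (12 per group) for 20% dropout and equal groups. The section also cites a 12-per-group rule for preliminary studies, based on feasibility, precision and regulatory considerations. It then states that the size will "offer enough statistical power to achieve the objectives".

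The Introduction makes synergy the primary aim and hypothesises that the combination gives "greater cognitive improvement in individuals with schizophrenia compared to" each treatment given alone. Section 2.11 names the synergy test: the mixed models carry the "HD-tDCS × CCRT interaction as a fixed effect". It adds a Bonferroni adjustment for evaluations at different time points. The Discussion opens its limitations with "Firstly, the relatively small sample size" and says that this might affect power.

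**The concern.** A power figure belongs to one test and one alternative. The figure here comes from an ANOVA F test, while the objectives rest on specific contrasts: a 2×2 interaction, and Group 1 against Group 2 and against Group 3. At a given visit the interaction contrast has one degree of freedom and twice the variance of a pairwise difference. The Bonferroni step is also absent from the stated alpha.

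Section 2.11 makes an affirmative statement about the objectives, so this is not a detail left to a separate analysis plan. At stake is how the primary result can be read. A non-significant interaction carries little information about synergy if its power was well below 80%, and the adequacy sentence invites a different reading.

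**Working it through.** **Inputs from the article.** Alpha 0.05, power 0.80, f = 0.25, N = 36 then 48, dropout 20% (section 2.11); four groups and four visits (section 2.1).

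**Assumptions, not in the article.** Correlation between visits r = 0.5, sphericity epsilon = 1, a Bonferroni divisor of 3 (T1, T2, T3), and the effect patterns below. SD means the between-patient SD at one visit. At r = 0.5 the SD of a change score is the same, because √(2(1 − r)) = 1.

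**1. Reproducing 36.** For the within-between interaction, λ = f²·N·m/(1 − r), df1 = (k − 1)(m − 1), df2 = (N − k)(m − 1). With k = m = 4:
- N = 36: λ = 0.0625 × 36 × 4/0.5 = 18, df 9 and 96, power 0.825.
- N = 48: λ = 24, df 9 and 132, power 0.939.
- The smallest N reaching 0.80 is 35, hence 36 for equal groups.

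Other options:
- A time test with four groups and two measurements also leads to 36 (power 0.829).
- A time test with four visits needs 24.
- The between-groups test needs 116 and has power 0.29 at 36.

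Dropout: 36/0.8 = 45, rounded to 48 for equal groups. This is correct.

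**2. What f = 0.25 means.** The effect is taken as absent at T0 and constant at T1–T3. In the 4×4 table, f is the root mean square of the interaction residuals divided by the SD. If only Group 1 gains δ, f = δ × 3/16, so δ = 0.25 × 16/3 = 1.33 SD. The same conversion gives:
- additive effects: each single therapy 0.82 SD, the combination 1.63 SD;
- each single therapy at one third of the combination: 0.53 and 1.59 SD.

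**3. Power of the objective tests at T2.** The contrast variance is c·v/n, with c = 4 for the interaction and 2 for a pairwise difference. v = 1 − r² = 0.75 when baseline-adjusted, and 2(1 − r) = 1 for change scores. Tests are two-sided with 4n − 4 residual df. Joint power to beat both single therapies is by simulation. For example, the interaction with Group 1 only, n = 12, baseline-adjusted: 1.333/√(4 × 0.75/12) = 2.667, power 0.74.

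Ranges run from 9 to 12 per arm:

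| Pattern | Test | Baseline-adjusted | Change scores | Baseline-adjusted, alpha 0.05/3 |
|---|---|---|---|---|
| Group 1 only, 1.33 SD | Interaction | 61–74% | 49–62% | 43–57% |
| Group 1 only, 1.33 SD | Beats both | 81–93% | 67–82% | 65–83% |
| 1.59 vs 0.53 SD | Interaction | 14–18% | 12–15% | below 10% |
| Additive, 0.82 SD each | Interaction | no synergy to detect | no synergy to detect | no synergy to detect |
| Additive, 0.82 SD each | Beats both | 33–46% | 23–34% | 18–28% |

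In the additive row the group-by-time F test keeps its 0.825 to 0.939 although synergy is zero. Its power therefore cannot be power for synergy.

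**4. Interaction averaged over T1–T3.** v = (1 + 2r)/3 − r² = 0.417 when baseline-adjusted. With a constant 1.33 SD effect confined to Group 1, power is 85–94%. With change scores, v = (1 + 2r)/3 + 1 − 2r = 0.667 and power is 66–79%.

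**5. Differences detectable with 80% power at T2, alpha 0.05 (12 to 9 per arm).**

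| | Interaction | Pairwise |
|---|---|---|
| r = 0.5, baseline-adjusted | 1.4–1.7 SD | 1.0–1.2 SD |
| r = 0.5, change scores | 1.65–1.9 SD | 1.2–1.4 SD |
| r = 0.8, baseline-adjusted | 1.0–1.2 SD | 0.7–0.8 SD |

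**The case against.** The strongest reply is that power is not low everywhere. If only the combination works, the chance of beating both single therapies is 81–93% before multiplicity, and an interaction averaged over T1–T3 can exceed 80%. That stands, and it rules out the reading that the trial is underpowered for every objective. Both results, however, need a gain of about 1.3 SD confined to one arm, which the article does not justify, and the averaged result also needs baseline adjustment.

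The option behind 36 is inferred. A reader might take the 9-df test as stated, but the article names neither the option nor r nor epsilon. The conclusion does not hinge on it, because neither reading that fits tests an objective.

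The Discussion already concedes that the sample is small. That is partial disclosure, but it conflicts with the sentence in section 2.11 and does not correct it. The 12-per-group rule supports feasibility and precision, not a power claim.

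A reader might also infer that the article promises a definitive answer, or plans to treat a non-significant interaction as absence of synergy. The Conclusion states only an aim to determine superiority, and no section sets such a rule. The risk lies in later interpretation.

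**Conclusion.** The adequacy sentence is not supported. The calculation that yields 36 powers a different hypothesis from those the article makes its objectives. For the interaction at T2, power stayed below 80% in every synergy pattern tried at f = 0.25 and r = 0.5: 61–74% at best when baseline-adjusted, and 14–18% when the single therapies also work. For superiority to both single therapies, the answer depends on the pattern, from 33–46% to 81–93% before any Bonferroni adjustment.

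The exact figures rest on the assumed r, the effect pattern, the choice between baseline adjustment and change scores, and a divisor of 3. A higher r shrinks the detectable differences, but at r = 0.8 the interaction still needs about 1.0–1.2 SD.

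It would be tempting to call this an arithmetic error. It is not: 36 reproduces under plausible settings, and the inflation to 48 is right. The fault is a mismatch between the powered test and the objectives.

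**What to change.** Keep 48 patients and revise the text:

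- In section 2.11, name the test, the number of measurements, the correlation and the epsilon behind N = 36. If it was the group-by-time F test with r = 0.5 and epsilon = 1, say that 36 and 48 patients give about 82.5% and 94% power for that test at f = 0.25.
- Delete or qualify the adequacy sentence, and reconcile it with the first limitation in the Discussion.
- State the differences detectable with 80% power at T2 for the interaction and for Group 1 against Group 2 or 3. Give the assumptions beside them: correlation, baseline adjustment or change scores, evaluable patients per arm, and before multiplicity. Step 5 of the working supplies figures for r = 0.5 and r = 0.8.
- Describe the synergy and pairwise results as preliminary, report estimates with 95% confidence intervals, and state that a non-significant interaction will not be taken as absence of synergy.

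The cost is wording only. No patients, visits or analyses are added, but the stated power becomes less favourable.

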to evaluate the robustness of our findings. Line charts will be employed to 
visualize the data, offering a clear depiction of outcome value trends across 
time points. Given the repeated-measures nature of the data, we will utilize 
statistical methods suitable for this design. In addition to the mixed-effects 
models, we will explore non-parametric repeated-measures approaches where 
applicable. These methods are suitable for analyzing between-group differences at 
specific time points and changes within groups over time for both primary and 
secondary outcomes. Moreover, the Likelihood Ratio Test will be used to 
specifically assess the effect of the therapy. The Bonferroni correction will be 
employed to adjust *p*-values, addressing the issue of multiple comparisons from 
evaluations at different time points.

To further elucidate the underlying mechanisms, we will conduct correlation 
analyses to investigate the relationships between alterations in neuroimaging 
metrics, serum levels of BDNF/GDNF, and cognitive performance scores in 
participants. Additionally, we intend to utilize mediation analysis models to 
assess whether intervention-induced changes in brain activity and/or BDNF/GDNF 
levels mediate improvements in cognitive outcomes. Moreover, we will perform an 
exploratory analysis of the CCRT metrics (e.g., task accuracy, reaction time) to 
compare cognitive performance during training between the HD-tDCS + CCRT group 
(Group 1) and the CCRT group (Group 3). This analysis could clarify the immediate 
neuroenhancing potential of concurrent HD-tDCS.

A stable antipsychotic medication regimen will be required for all patients, 
requiring consistent dosing for a minimum of two weeks prior to the trial and 
maintaining this regimen unchanged throughout the study period. This protocol 
will be implemented to minimize confounding effects on clinical outcomes, in 
accordance with recommendations from previous literature [52]. The Defined Daily 
Dose (DDD) methodology will be utilized to standardize antipsychotic medication 
doses across study groups. This involves converting administered doses into DDD 
units following randomization to ensure pharmacological equivalence. To account 
for dosing variability and maintain the accuracy of results, DDD values will be 
incorporated as a covariate in all statistical models. All collected data will be 

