entered into a database and analyzed using SPSS version 20.0 (IBM Corp., Chicago, IL, USA). Significance is 
defined as *p *
< 0.05.

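### The likelihood ratio test named for the therapy effect is mildly anti-conservative with 12 patients per arm: about 6-8% actual size at a nominal 5%, if the usual chi-square reference is used (minor point)

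*Protocol article*

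**What the plan says.** All of this stands in section 2.11 of the protocol article.

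- The analysis uses linear "mixed-effects models. These models are appropriate for making valid inferences" under missing at random, on the intention-to-treat principle. Synergy enters as the HD-tDCS × CCRT "interaction as a fixed effect".
- For the therapy effect, "the Likelihood Ratio Test will be used to" "specifically assess the effect of the therapy". No other test is tied by name to that purpose.
- DDD values are to be "incorporated as a covariate in all statistical models".
- The target is 48 "participants, with 12 participants per group". The sample-size calculation sets the "probability of a Type I error (α) at 0.05", and significance is declared at p < 0.05.
- The data are to be "entered into a database and analyzed using SPSS version 20.0".

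The section does not give the reference distribution of the likelihood ratio test, the covariance structure or the tested term. Section 2.1 gives four assessments, T0 to T3.

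**The concern.** A likelihood ratio test of fixed effects, referred to chi-square, is justified in large samples. It takes no account of the degrees of freedom spent on fixed effects or of the uncertainty in the estimated variances. With four arms, a covariate and 48 patients at most, both matter a little. The error goes one way: p-values are too small, so an effect of therapy is declared slightly more often than the stated 5% allows. The sample size was itself derived from an F-test, so the plan is powered on one reference distribution and names a test that normally uses another.

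**Working it through.** **The plan's own figure.** Inputs from section 2.11: f = 0.25, α = 0.05, power 0.80, repeated-measures ANOVA. Assumed: the within-between interaction, 4 groups × 4 visits, correlation 0.5 and sphericity (ε = 1).

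- Noncentrality λ = f² × m/(1 − ρ) × N = 0.0625 × 4/0.5 × 36 = 18, on (9, 96) degrees of freedom: power 0.825.
- N = 32 gives 0.762, so 36 reproduces. Then 36/0.8 = 45, rounded up to four equal groups = 48.

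The sample size is not at issue here.

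**Size of the test, closed form.** For complete balanced data, the maximum-likelihood statistic for a term with q degrees of freedom is LR = n × ln(1 + qF/d). Here F has an exact F(q, d) distribution under the null. Rejecting when LR exceeds the chi-square 5% point c is therefore the same as rejecting when F exceeds (e^(c/n) − 1) × d/q.

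- *1-df HD-tDCS × CCRT term, N = 48:* n = 48, d = 44, c = 3.841. Cut-off F = (e^(3.841/48) − 1) × 44 = 3.67, against a correct 4.06. Size 6.2%.
- *The same with DDD as covariate:* d = 43, cut-off 3.58 against 4.07. Size 6.5%.
- *HD-tDCS × CCRT × time, 3 df, random intercept:* n = 48 × 3 = 144, d = 44 × 3 = 132, c = 7.815. Cut-off 2.45 against 2.67. Size 6.6%.
- *Group × time, 9 df, random intercept:* n = 144, d = 132, c = 16.919. Cut-off 1.83 against 1.95. Size 6.9%.

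**Unstructured covariance.** Here LR = −N × ln(Wilks' Λ) on the three time contrasts, evaluated with 400,000 draws.

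| Test | N = 48, random intercept | N = 48, unstructured | N = 36, random intercept | N = 36, unstructured |
|---|---|---|---|---|
| HD-tDCS × CCRT × time (3 df) | 6.6% | 7.5% | 7.3% | 8.6% |
| Group × time (9 df) | 6.9% | 8.3% | 7.6% | 9.7% |

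The 1-df between-patient term at N = 36 is 6.7%, or 7.1% with DDD.

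**Check under the planned kind of analysis.** The random-intercept model with DDD was simulated for 48 patients (6,000 trials per setting, standard error about 0.3 points). Across the tests examined, size was 6.2-7.4% without dropout and 6.3-7.8% with 20% monotone dropout.

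**The alternative.** In the balanced random-intercept case the F reference has size exactly 5%. Under unstructured covariance, the multi-df Wald F with N − 4 denominator degrees of freedom has simulated size 5.8-5.9% at N = 48 and about 6.1% at N = 36.

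**The case against.** The best defence is that the article is condensed. It does not say that the statistic is referred to chi-square, and details of that kind commonly sit in a fuller plan. The test is also introduced as an addition to mixed models that already carry the interaction, so other tests of therapy may be reported beside it. Both points are fair, and they make the finding conditional. They do not remove it: the article names this test for this purpose, chi-square is its standard reference, and no alternative is mentioned.

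A reader might infer more than the documents support:

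- *That 12 per arm means an error rate up to 10%.* Figures near 10% belong to 36 complete cases, which is 9 per arm, with unstructured covariance and the 9-df test. The planned analysis keeps the observed visits of dropouts, and 20% loss from 48 leaves about 38 completers (48 × 0.8 = 38.4). A joint 12-df test of group and group × time would reach 9.4% at N = 48 under unstructured covariance, but the plan names no such test.
- *That the test is invalid because REML likelihoods are compared.* The article does not say how the models are fitted, so nothing in it supports this.
- *That the inflation compounds with the Bonferroni step or with uncontrolled multiplicity.* Section 2.11 links Bonferroni to evaluations at different time points. It gives no number of comparisons and does not say that likelihood ratio p-values are adjusted. Any figure at an adjusted level would rest on an invented count.

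**Conclusion.** The point holds in a limited form. If the likelihood ratio test is referred to chi-square, its actual size at nominal 5% is about 6-8% with 48 patients. The low end applies to the 1-df synergy term and the high end to the 9-df test with unstructured covariance. Every setting examined lies above 5%. Which figure applies depends on the covariance structure and tested term, neither of which the article fixes, so no single figure is the plan's error rate. The excess is modest, about 1 to 3 percentage points, and would matter mainly for a result near the threshold. This is a minor point with an almost free remedy.

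**What to change.** In section 2.11, replace the sentence on the likelihood ratio test with one stating that the therapy effect is assessed by the F or t test of the named contrast, from the REML mixed model with Satterthwaite degrees of freedom, and reported with the 95% confidence interval from the same fit. SPSS MIXED provides this, so no new software, data or patients are needed. It also brings the test closer to the F-test behind the sample size. The cost is slightly larger p-values. The correction is not perfect: with an unstructured covariance a multi-df test would still have a size of about 6%.

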## 2. Methods

### 2.1 Study Design 

This study is a prospective, double-blind, randomized controlled trial protocol 
to assess the efficacy of HD-tDCS combined with CCRT in enhancing cognitive 
function among patients with schizophrenia. Eligible participants will be 
recruited and randomly allocated into four groups using a random number table: 
the HD-tDCS + CCRT group (Group 1), the HD-tDCS group (Group 2), the CCRT group 
(Group 3), and the control group (Group 4). Assessments will be carried out at 
baseline (T0), after 10 sessions (T1), after 20 sessions (T2), and after six 
months of follow-up (T3). Research framework is illustrated in Fig. 1. 
Participants in the control group (Group 4) will continue to receive their stable 
regimen of antipsychotic medication and standard clinical care, without 
undergoing any HD-tDCS or CCRT sessions.

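### Bonferroni across visits is valid, but Holm's step-down correction over the same comparisons never rejects less at the same familywise error

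*Protocol article*

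**What the plan says.** Section 2.11 (Statistical Analysis Plan) of the protocol article fixes the method in one sentence, directly after naming a likelihood ratio test to "specifically assess the effect of the therapy. The Bonferroni correction will be" used on the p-values, with the stated purpose of "addressing the issue of multiple comparisons from" assessments at the various visits. The divisor is not given. Section 2.1 lists the assessments as "baseline (T0), after 10 sessions (T1), after 20 sessions (T2), and after six" months of follow-up (T3), which makes three post-baseline visits.

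The same section names the main tests separately. Synergy is tested through the HD-tDCS × CCRT interaction in a linear mixed model, and the therapy effect through a likelihood ratio test. The sample size rests on a repeated-measures ANOVA F-test, for which the authors "established the probability of a Type I error (α) at 0.05, the" power at 0.80 and the effect size f at 0.25. This gives 36 participants, raised to 48 (12 per group) for 20% dropout.

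The Discussion lists the small sample as a limitation that "might influence the statistical power and limit the generalizability of the" results.

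**The concern.** Most choices of analysis trade one property for another. For adjusted p-values this one trades almost nothing. Single-step Bonferroni holds every comparison to 0.05/m, where m is the number of comparisons, whatever the other comparisons show. Holm relaxes the threshold after each rejection at no cost in familywise error.

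The difference matters when an effect must be shown at more than one visit. This trial wants that: the second aim in the Introduction is the six-month effect, Section 3 plans between-group comparisons at specific time points, and the Conclusion asks whether the combination gives more sustained benefit. With 12 patients per arm there is little power to spare.

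**Working it through.** **1. The plan's own figure.** The inputs from Section 2.11 are f = 0.25, α = 0.05, power 0.80 and 4 groups; Section 2.1 gives 4 assessments. Assumed, because not stated: correlation 0.5 and sphericity (ε = 1). For the within-between interaction, λ = f² × N × 4/(1 − 0.5), with df 9 and 3(N − 4).
- N = 36: λ = 0.0625 × 36 × 4/0.5 = 18, df 9 and 96, power 0.825.
- N = 32: λ = 16, df 9 and 84, power 0.762.

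So 36 reproduces. Then 36/0.8 = 45, rounded up to a multiple of 4, is 48. This is one omnibus test at 0.05, so the visit-wise correction plays no part in it.

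**2. Thresholds.** With m comparisons, Bonferroni uses 0.05/m for each. Holm compares the ordered p-values with 0.05/m, 0.05/(m − 1), …, 0.05 and stops at the first failure. For an assumed m = 3, that is 0.0167 three times against 0.0167, 0.025 and 0.05.

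**3. Why Holm never does worse.** Any p-value at or below 0.05/m, and every smaller one, passes all of Holm's steps up to that point, so Holm rejects everything that Bonferroni rejects. For error control, suppose m₀ nulls are true. The first true null to be rejected meets a threshold no larger than 0.05/m₀, so the familywise error is at most m₀ × 0.05/m₀ = 0.05, whatever the dependence between visits.

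**4. Size of the gain.** One contrast between two arms is tested two-sided at three visits, with 12 per arm, a common variance estimate on 48 − 4 = 44 df, between-visit correlation 0.5 or 0.7, and 200,000 simulated sets. The noncentrality at each visit is d/√(2/12). As a check at d = 0.8: 0.8/0.408 = 1.96 against a critical t of 2.489 gives 31% per visit under Bonferroni, matching the simulation.

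| True difference, every visit | Per visit, Bonferroni v Holm | All three visits, Bonferroni v Holm |
|---|---|---|
| 0.5 SD | 11% v 13–14% | 2–4% v 5–8% |
| 0.8 SD | 31% v 36% | 11–16% v 22–27% |
| 1.0 SD | 49% v 56–57% | 25–31% v 41–46% |

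Less favourable cases:
- Global null: familywise error is the same for both methods, about 4.4% at correlation 0.5 and 3.8% at 0.7.
- At least one significant visit: identical by construction, because Holm's first step is Bonferroni (53% for both at 0.8 SD, correlation 0.5).
- Effect of 0.8 SD at one visit only: 31% v 31% at that visit.
- Fading effect (0.4, 0.8, 0.2 SD): 31% v 31–32% at the peak visit.
- Nine per arm, as after the planned dropout: 8% v 10% per visit at 0.5 SD; 15–19% v 27–32% for all three visits at 1.0 SD.

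**The case against.** The strongest reply is that nothing is wrong. Bonferroni is pre-specified, controls the familywise error (1 − (1 − 0.05/3)³ = 0.049 for three independent tests), and the protocol makes no claim about its power. That stands: this is an improvement, not an error.

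A reader might also infer three stronger points that the documents do not support.
- *That the protocol holds each visit to 0.05/3.* It gives no divisor. Section 2.11 covers both between-group differences at time points and within-group changes, so the family may be larger than three. The argument for Holm holds for any m; the figures above do not.
- *That power is lost at every visit whatever the pattern of effect.* It is not. The first rejection faces the same threshold under both methods, and the gain nearly vanishes with an effect at one visit. Effects of 0.8–1.0 SD sustained to six months are a favourable case for Holm, and the Introduction itself doubts that stimulation effects last. If the planning value ("with an effect size (f) of 0.25") is read as a two-group difference of 2f = 0.5 SD, which is only a rough conversion for this design, the gain per visit is 2 to 3 percentage points.
- *That the small-sample limitation in the Discussion counts against Bonferroni.* That passage concerns the number of patients. The sample size and the interaction test do not depend on the correction.

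Bonferroni does keep one advantage: simple simultaneous confidence intervals that agree with its tests. Section 2.11 applies the correction to p-values, so the advantage is limited, but it is real.

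**Conclusion.** The point holds as a low-priority improvement. For adjusted p-values over the same comparisons, Holm gives the same error guarantee and at least as many rejections. With an effect at every visit, the gain is 2 to 3 percentage points per visit at 0.5 SD, about 5 at 0.8 SD and 7 to 8 at 1.0 SD. It is larger for showing all three visits: roughly 11 points at 0.8 SD and 15 to 16 at 1.0 SD. There is no gain in the chance of finding any significant visit.

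The dominance itself needs no assumptions. The sizes rest on three comparisons, two-sided tests, the stated correlations and the assumed effects, none of which the protocol gives for visit-wise tests. Holm does not rescue an underpowered comparison: at 0.5 SD power stays very low under either method.

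**What to change.** In Section 2.11, replace the Bonferroni correction with the Holm step-down (Holm-Bonferroni) correction over the same m time-point comparisons. Compare the ordered p-values with 0.05/m, 0.05/(m − 1), …, 0.05, stop at the first failure, and report Holm-adjusted p-values. Make the change before the data are locked and the first stage of unblinding in Section 2.4 begins.

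The cost is one sentence, plus a hand calculation if the software has no Holm option. Holm has no equally simple matching simultaneous intervals. Any Bonferroni intervals shown alongside should be labelled as such, because one may occasionally include zero when the Holm-adjusted p-value is significant. Nothing changes in the sample size, the data collected or the main model.
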